### Procedure

The COMPAS study plans to recruit in the experimental group individuals diagnosed with dementia and their caregivers receiving case management from different regional case management models in the Netherlands. Case managers provide lists of patients who are eligible to participate. Potential participants receive written information about the project either via a letter from the research coordinator or via the case manager who approaches them with information directly, asking them if they agree to be contacted by a researcher with more detailed information on the study. Potential participants can either mail (a pre-stamped envelope is attached to the written information) or call the research coordinator or the case manager to let him/her know that they are interested in this additional information. Subsequently, the interviewers call the potential participants to inform them about the study in more detail and to set an appointment for the baseline interview with those who are willing to participate. Interviewers also call participants who have not replied within two weeks after the letter is sent to see if they are interested to participate in the study. For the usual care participants, who do not receive case management, recruitment occurs via outpatient geriatric or neurologic (memory) clinics, Alzheimer centers and general practices where a letter is sent to ask them to participate followed by a phone call from the interviewers to ensure that the letter was received and to provide more information on the study.

Prior to the interviews, all participants will sign an informed consent form. Patients and caregivers are interviewed at their homes by trained research interviewers using case record forms. The cost diary is left at the house, collected during the next interview session, and a new cost diary is provided for the upcoming six months. All outcomes are measured at baseline, 6, 12, 18 and 24 months via questionnaires and interviews. Information on the dementia diagnosis is gathered from the informal caregiver. The caregiver is asked when first symptoms were detected and time of diagnosis. Recruitment started in March 2011. All people currently in case management are screened for eligibility and asked to participate. Data collection is expected to end in 2014.

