	Time between first symptoms and institutionalization	Economic evaluation	X	X	X	X	X
Effect modifiers or confounders	Age		X				
	Gender		X				
	Marital status		X				
	Living accommodation	Living alone or with someone	X				
	Education		X				
	Mini Mental State Exam [49]	Cognition	X		X		X
	KATZ Activities of Daily Living-5 [50]	Activities of daily living*	X	X	X	X	X
	Co-morbidity		X				
	Dementia type		X				
	Time in case management		X				
Caregiver							
Primary outcomes	General Health Questionnaire −12 [38]	Emotional stress mental health complaints	X	X	X	X	X
Secondary outcomes	Short Sense of Competence Questionnaire SSCQ [51]	Perceived care competence	X	X	X	X	X
	Pearlin Mastery Scale [52]	Self-efficacy	X	X	X	X	X
	EuroQol 5D[53]	Health related quality of life	X	X	X	X	X
	Carer-Qol [54]	Health related quality of life	X	X	X	X	X
	SF12 [46]	Health related quality of life	X	X	X	X	X
Cost outcomes	Informal care	Economics evaluation	X	X	X	X	X
Quality of care	Quality indicators [43,55]	Process of Care	X	X	X	X	X
Effect modifiers or confounders	Age		X				
	Education		X				
	Relation to person with dementia		X				

*by proxy, **patient and proxy.

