### Effect evaluation

Data will be analyzed by the intention to treat principle. Propensity score techniques will be used to address potential selection bias [60]. The propensity score is a one-dimensional summary measure that is directly related to the predicted probability that a subject with specific baseline characteristics is included in the intervention group (relative to the control group) [60]. Propensity scores are derived as the fitted linear predictor values from a logistic regression model with treatment (per case management model versus usual care) as the outcome variable. All variables on which groups differ at baseline are included as covariates. Depending on the mismatch of the intervention and control group on these propensity scores we will use 1-to-1 matching, stratified (quintile) matching or choose to include the propensity score as a confounder in the regression models for treatment effects [61].

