At the regional level, confounding by socio-economic differences may limit the internal validity of the comparisons. This will be corrected for by using socio-economic characteristics of the patients (e.g. education), demographic factors (e.g. age and marital status) and by checking for clustering at the regional level in the multilevel analysis. The case management models may differ in their development (some regions started case management recently while others already exist for ten years), referral modality, the case loads of case managers and their funding, causing within and across case-management model type heterogeneity, which could have an effect on the care received by the person with dementia and their carer. A description of each model will help identify differences. The risk of selection bias potentially occurs at the patient level. Firstly, there may be confounding by indication and confounding by severity of cognitive impairments, as the likelihood of referral to case-management by a general practitioner may depend on patient characteristics, such as severity of dementia. Potential confounders include demographics like age, gender, education of patients and caregivers, time in case management, dementia severity (MMSE, dementia-type and caregiver burden (Sense of Competence questionnaire [51]). Baseline characteristics of the patients in the three intervention groups will be compared and post-hoc matching techniques and stratification will be used when necessary [39]. In a secondary analysis, semi-structured interviews with a random sample of general practitioners will be performed to identify reasons for case management referral and, thus, to identify potential selection bias. Secondly, in our opinion, there is a risk of only recruiting dementia caregivers who experience relatively less burden, limiting the external validity of the study. A non-responder analysis will be completed to identify this source of potential bias and matching techniques will be used to correct for variables such as severity of cognitive impairments (MMSE), time since diagnosis and age and health of the person with dementia and caregiver.

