Attrition bias will also be analysed as an increase in severity of the disease (and therefore burden of disease). This will probably predict drop-out, leading to ‘survival’ of a relatively healthy population for the intention to treat analysis. The solution is to rigorously retrieve information on drop-outs, for example in cases where the caregiver or care receiver has died or was institutionalized. Proxy measurements will be used when the care receiver refuses or is not able to completely answer the questions in order to avoid missing data. The caregiver will act as the proxy. Proxy measurements will be used for the EQ-5D, CANE and QoL-AD. As case management is growing quickly in the Netherlands, recruiting unexposed client dyads may be a serious problem. If it appears to be impossible to recruit enough controls, then only the different case management groups will be compared against each other. A more general problem is recruiting enough people to participate, and subsequently to maintain them, in the study. As this is a burdened population that is also frequently recruited for other studies, recruiting dyads for this study is challenging and attrition rates may be high. We plan to address this in two ways. First, we must explain to participants the importance of this research as it identifies who benefits from case management and who may not and it will endeavour to determine the most efficient model. Secondly, we made every effort to avoid burdening the caregivers with unnecessary interviews or questions. An important limitation might be a relatively low participation rate that fuels confounding by indication and hinders adequate stratified analyses. As all potential participants were approached at the full time spectrum since diagnosis (except for an expected institutionalization within 6 months), an important assumption is, that the effectiveness of case management is constant over time. However, a review by Pimouguet et al. [29] found an early time effect on case management under a year and then less of an effect later on. We will handle this by using time in case management as a covariate to correct for differences between subjects in the groups. The generalizability of the results for clinicians and policy makers will largely depend on achieving the sample size required, the homogeneity of the population samples and our ability to adequately correct for potential confounders and effect modifiers in the statistical analyses. Despite the limitations addressed here, we expect that this study will provide important information on dementia case management models in The Netherlands for policy makers, health care providers, patients and informal caregivers.

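### Time in case management is named as a confounder without limiting it to the comparison of the two case management models, although it is zero or undefined in usual care

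*Protocol article*

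**What the plan says.** All references are to the protocol article.

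- **Discussion, on non-constant effectiveness.** The article assumes that the effect of case management does not change over time. It then cites a review that found an effect within the first year and a smaller one later. Its answer is: "We will handle this by using time in case management as a covariate to correct for differences between subjects in the groups".
- **Discussion, on confounding by indication.** "Potential confounders include demographics like age, gender, education of patients and caregivers, time in case management", followed by dementia severity and caregiver burden.
- **Table 2.** "Time in case management" is a baseline-only variable in the patient block for effect modifiers or confounders.
- **Effect evaluation.** The propensity score comes from a "logistic regression model with treatment (per case management model versus usual care) as the outcome variable". The covariate rule is "All variables on which groups differ at baseline are included as covariates". The score is then used in one of three ways: "we will use 1-to-1 matching, stratified (quintile) matching or choose to include the propensity score as a confounder in the regression models".
- **Usual care and Procedure.** Usual care participants do not receive case management. The case management groups are drawn from people already in it.
- **Procedure, on disease stage.** "The caregiver is asked when first symptoms were detected and time of diagnosis".

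**The concern.** Time in case management measures how much of the exposure a person has had. In the two case management groups it is positive for nearly everyone; in usual care it is zero or does not exist. It therefore cannot confound case management against usual care, because it is part of what is being compared.

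The first hypothesis is exactly that comparison. An analyst who follows the text could put the variable into either of two models, and in each it does harm. In the propensity model it identifies the group. In the outcome regression it changes what the group coefficient estimates, or at best makes it less precise. The rule under Data analyses to report confounders that move a coefficient by more than 10% would not protect against this: a large shift caused by extrapolation would look like important confounding.

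**Working it through.** **1. The plan's own figure.** Inputs from Sample size: NPI difference 5.2, SDs 13.7 and 20.3, within-subject correlation 0.5, one-sided alpha 0.05, 140 per group.

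- SD of change = SD × sqrt(2(1 - 0.5)) = SD, so 13.7 and 20.3.
- SE of the difference = sqrt((13.7² + 20.3²)/140) = sqrt(599.78/140) = 2.07.
- The Satterthwaite test needs 138 per group for 80% power; at 140 the power is 80.5%. The stated 140 reproduces and is not in dispute.

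**2. Propensity model.** Suppose time T is entered with usual care at 0. Anyone with T > 0 is certainly in case management, so the likelihood keeps rising as the coefficient of T grows and no finite estimate exists. A trial fit with 140 per group failed with a singular matrix. It failed again with 10% or 30% of case management participants at T = 0 (quasi-complete separation), where only those few could resemble a control. Without T the same models converged, and 95% to 100% of case management participants lay within the control range of scores. If T is coded missing in usual care instead, a complete-case fit drops every control.

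**3. Outcome regression, what the coefficient means.** Take Y = a + b·group + c·T with T = 0 in usual care. Usual care fixes a, and the slope c comes from the case management group alone. Hence

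b = (mean difference) - c × mean(T),

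which is the case management line read off at T = 0.

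*Effect that varies with time.* Assume -5.2 in year one, 0 afterwards, and T uniform on 0-4 years.

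- Mean(T) = 2; var(T) = 16/12 = 1.333.
- True average effect = -5.2 × 1/4 = -1.3.
- Cov(T, effect) = (-5.2 × 1/4 × 0.5) - 2 × (-1.3) = -0.65 + 2.6 = 1.95.
- c = 1.95/1.333 = 1.46 per year.
- b = -1.3 - 2 × 1.46 = -4.2. Simulation agrees.

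Two milder shapes, simulated with exponential times of mean 2 years, shift in the same direction:

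| Assumed effect | True average | Coefficient with T |
|---|---|---|
| -8, shrinking by 1.4 per year | -5.2 | about -8.0 |
| -8 in year one, -3 later | -5.0 | about -6.5 |

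Centring T at its mean within the case management group, with usual care at 0 after centring, brings the coefficient back to the average effect in both rows (-5.2 and -4.9).

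**4. Outcome regression, precision when the effect is constant.** Then c = 0 in expectation and b is unbiased. Ordinary least squares reports

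SE = sqrt( (s²/n) × (2 + mean(T)²/var(T)) ), with s² = 599.78/2 = 299.89 and s²/n = 2.142.

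| Assumed T | mean²/var | Reported SE, formula | Simulated mean SE | Sampling SD of b |
|---|---|---|---|---|
| Exponential | 1 | sqrt(2.142 × 3) = 2.54 | 2.55 | 2.37 |
| Uniform 0-4 years | 3 | sqrt(2.142 × 5) = 3.27 | 3.29 | 2.88 |

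The sampling SD is sqrt((13.7² × (1 + mean²/var) + 20.3²)/140). It is below the reported SE because the pooled variance is too large for the less variable case management group. The test uses the reported SE, so with critical value 1.65:

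- Exponential: (5.2 - 1.65 × 2.54)/2.37 = 0.43, power about 66%.
- Uniform: (5.2 - 1.65 × 3.27)/2.88 = -0.07, power about 47%.

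Simulation of the ordinary test gives the same figures. Without T the power is about 80%.

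**The case against.** Four points deserve weight.

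- **The propensity model does not name the variable.** A reader might infer that the planned model is bound to fail. Effect evaluation does not say so: entry follows only from joining its general covariate rule to the confounder lists in Table 2 and the Discussion. A failed fit would also be noticed and the variable dropped. This stands, and the propensity point is therefore conditional.
- **The covariate has a proper use.** The study also compares the two case management models with each other, and will compare only those if too few controls can be recruited. There the variable exists in both groups and is a valid covariate. Table 2 also leaves open the role of effect modifier. This stands too, but no sentence confines the variable to these uses, and the confounding paragraph in which it is listed concerns referral to case management.
- **The regression is not always biased.** A reader might infer that any adjustment distorts the effect. It does so only if the effect varies with time and an uncentred term is used with usual care at 0. The article fixes no coding, and under its own constancy assumption only precision is lost. But the covariate is offered precisely because the article doubts constancy.
- **The covariate is not offered for disease stage.** A reader might infer that it is the plan's remedy for unequal stage, or for its main weakness. The Discussion offers it for non-constant effectiveness, does not rank that problem first, and handles severity and time since diagnosis elsewhere.

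**Conclusion.** The point holds as a matter of scope and wording. The article names time in case management as a confounder and covariate with no limit on where it applies, and in the usual-care contrast it cannot do that job. The structural part needs no assumption beyond its being zero or undefined in usual care: separation if it enters the propensity model, extrapolation to time zero if it enters the regression linearly with controls at 0.

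The sizes are illustrations. The article gives no distribution of time in case management, so exponential and uniform 0-4 year times are assumed, as are the effect shapes. The shift from -1.3 to about -4.2 further assumes no effect at all after the first year, which is stronger than the smaller later effect the article reports; milder shapes give smaller proportional shifts. The power loss from about 80% to about 66% or 47% applies to a constant effect of -5.2. This should be settled before analysis because it touches the primary contrast.

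**What to change.** 1. State that time in case management is excluded from every propensity model and every regression that contrasts case management with usual care, and make it an explicit exception to the covariate rule in Effect evaluation.
2. Use it only as a covariate in linkage versus intensive/joint agency, or as an effect modifier within the case management groups (for example centred within those groups). The second use answers the doubt about constant effectiveness directly.
3. In the usual-care contrast, adjust for time since diagnosis, which the Discussion already names for matching, and for time since first symptoms.

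The cost is a few sentences of analysis text. No new data are needed: according to Procedure, caregivers are asked for both dates. The sample size calculation is unaffected.
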